## 809 **2.7 Hypothesis framework**

810 For each of the primary and secondary outcomes, the null hypothesis will be that there is no true difference  
811 in effect between the intervention arms.

812

## 813 **2.8 Sample size**

814 The annual number of visits to the pediatric emergency room at Oulu University Hospital is about 4,000–  
815 5,000; of these, about 50–70% are related to infections. The main outcome measure in the study is the  
816 number of antibiotic treatment courses initiated. We estimate that according to current treatment  
817 practice, treatment with antibiotics is started in about 25% of acutely sick children with fever in the  
818 emergency room at Oulu University Hospital. A relative reduction of 25% in the number of antibiotic  
819 treatment courses initiated was estimated as the lowest clinically significant reduction in antibiotic therapy.  
820 In the review of Doan et al. [1] (2014), a 25% reduction in antibiotic therapy and hospital treatment was  
821 considered clinically significant as well.

822

823 When the subjects were randomized to groups at a 2:1 ratio, assuming  $\alpha$  error probability of 0.05 and  
824 power (type 1 $\beta$  error) of 0.8, a sample size of 1,062 subjects in the intervention group and 531 in the  
825 control group is needed, resulting in a total sample size of 1,593 subjects. In view of dropouts, we will  
826 recruit an additional 50 subjects to the new intervention group and 25 subjects to the control group,  
827 yielding a total number of 1,668 subjects recruited.

828 Some patients revisit the emergency room and they can be recruited again if the clinical picture has  
829 deteriorated significantly or a new illness is suspected, but only first visits are included in the targeted  
830 sample size.

831

832 It is estimated that gathering of data will take 12 months, and the trial ends when the full sample size is  
833 reached. If the targeted sample size is reached before 12 months, data gathering will continue for a total of  
834 12 months to achieve a sample that covers a whole epidemiological year. No interim analyses will be made.

835

836 The original precise calculation was made using StatsDirect 3 software:

837

838 Sample size for independent cohort study

839 Probability of event in control group = 0.25

840 Probability of event in experimental group = 0.1875

841 Controls per case subject = 0.5

842 Alpha = 0.05

843 Power = 0.8

844 For uncorrected chi-square test: N = 1,014 case subjects and 507 controls

845 For corrected chi-square and Fisher's exact tests: N = **1,062** case subjects and **531** controls

846

847 Due to the current pandemic, the statistical power was calculated based on the data about antibiotic  
848 consumption in study population to decide whether to complete or discontinue the study due to Covid-19  
849 pandemic. On Feb 18, 2020, in the study database, antibiotics had been prescribed in 30.4% of children  
850 (about 700 children). No interim analysis was performed. At the time it was estimated that the proportion  
851 of children with antibiotic prescriptions would be higher in the control group, about 33%. By using the  
852 baseline proportion 33% in the control group, and with the same relative reduction of 25%, we calculated  
853 the final sample size.

854

855 A new calculation of the sample size required was made (Feb 18, 2020) using StatsDirect 3:

856

857 Sample size for independent cohort study

858

859 Probability of event in control group = 0.33

860 Probability of event in experimental group = 0.25

861 Controls per case subject = 0.5

862 Alpha = 0.05

863 Power = 0.8

864

865 For uncorrected chi-square test: N = 747 case subjects and 373 controls

866 For corrected chi-square and Fisher's exact tests: **N = 785 case subjects and 392 controls (1177**  
867 **children in total)**

868

869 Missing data were rare due to comprehensive medical records in the hospital and in the national registers.  
870 **Based on the calculation, the sample size reached was considered sufficient in terms of statistical power**  
871 **even if the randomization had to be stopped prematurely.**

872

## 873 **2.9 Randomisation and blinding**

874 The study is a single-center open label clinical trial, randomization is done in 2:1 permuted blocks, the size  
875 of which varies randomly between 3, 6, and 9. The randomization is done using computer-generated  
876 random sequence numbers by a biostatistician not involved in data gathering. The biostatistician draws up  
877 a list of numbers. After this, a study nurse who is not involved in the trial or data gathering places the  
878 interventions in non-transparent envelopes with a running trial number (1-1668). After randomization, the  
879 study is an open study, because the outcome measures compared are not subjective but data collected  
880 from medical records, and randomization would not be relevant in this setting. Trial design did not enable  
881 blinding.

882

## **2.11 Trial reporting**

The trial will be reported according to the principles of the CONSORT statements.

## **3 ANALYSIS POPULATIONS**

### **3.1 Population definitions**

The intention to treat (ITT) population will be all participants randomised, irrespective of intervention received.

No interim analyses are performed.

## **4 DESCRIPTIVE ANALYSES**

### **4.1 Participant throughput**

The flow of participants through the trial will be summarised using a CONSORT flowchart. The flowchart will describe the numbers of participants randomly allocated, who received allocation, withdrew consent, and included in the ITT analysis population.

### **4.2 Baseline characteristics for randomized groups**

The following characteristics will be described separately for patients randomised to each arm. Differences between groups are not tested statistically.

#### 4.3 Completeness of follow-up

Loss to follow-up is expected to be minimal as the most of data for primary and secondary outcomes is manually collected from routine clinical data.

#### 4.4. Protocol violations or deviations

Protocol violations are classed and reported as follows [3]:

1) **Enrolment PVs** occurred when a member of the research team failed to appropriately apply the study's eligibility criteria resulting in the enrolment of an inappropriate patient into the trial.

a. *Did not fill inclusion criteria*

b. *Hospitalized patient recruited*

2) A **randomisation PV** was defined as a technical or human error leading to the violation of the intended randomisation sequence or any attempts to subvert allocation concealment.

a. **Intended randomization failed**

3) A **study intervention PV** was defined as a dosing, timing or delivery error in the study intervention attributable to members of the research team. The research team included members of the study coordinating centre, site investigators, research coordinators and members of the healthcare team caring for participants.

a. **The sample taken from the participant in the control group was analyzed immediately**

b. **Technical error of the diagnostic device**

c. **No sample taken from the participant in the intervention group**

4) A **patient compliance PV** involved study participants failing to comply with the trial protocol regarding a study intervention or other requirements of participation in the trial (e.g. skipping

scheduled appointments). Formal withdrawal of consent to participate was not considered a patient compliance PV.

**5) Data collection PVs** encompassed errors in which the research team failed to comply with pre-specific trial guidelines for data collection and/or outcome evaluation due to avoidable reasons.

## **5 COMPARATIVE ANALYSES**

For all outcomes, the primary analysis will be performed on the intention to treat (ITT) population. Pairwise comparisons for each outcome between randomization arms will be reported.

### **5.1. Primary outcome**

The counts and proportions of participants to receive antibiotic prescription at ED will be reported. To analyze the primary outcomes, we will calculate 95 % confidence intervals (CI) of the differences using a Standard Normal Deviate (SND) test for the proportions. Risk ratios (RR) with 95 % CI are calculated.

### **5.2. Secondary outcomes**

#### **5.2.1. Antibiotic prescription within 7 days after study entry**

The counts and proportions of participants to receive antibiotic prescription at ED and during following 7 days will be summarized and reported. To analyze the primary outcomes, we will calculate 95 % confidence intervals (CI) of the differences using a Standard Normal Deviate (SND) test for the proportions. Risk ratios (RR) with 95 % CI are calculated.

#### **5.2.2. Macrolide antibiotic prescriptions at ED**

The counts and proportions of participants to receive macrolide antibiotic prescription at ED will be reported. To analyze the primary outcomes, we will calculate 95 % confidence intervals (CI) of the differences using a Standard Normal Deviate (SND) test for the proportions. Risk ratios (RR) with 95 % CI are calculated.

**5.2.3. Macrolide antibiotic prescriptions in infants aged under 3 months**

The counts and proportions of infants aged under 3 months to receive macrolide antibiotic prescription at ED will be reported. To analyze the outcome, we will calculate the proportion difference with 95 % confidence intervals (CI) using a Standard Normal Deviate (SND) test for the proportions. Risk ratios (RR) with 95 % CI will be calculated.

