**Subjects are recruited for the trial by a pediatric emergency room nurse upon emergency room registration.** The emergency room nurses have previous experience of recruiting patients from two clinical trials. The subjects recruited to the study can also discuss the trial with the on-call physician. The subjects are asked to provide a written consent, after which they are randomized into groups in a 2:1 ratio (treatment under study:current treatment). The interventions are randomized by trial numbers and enclosed in non-transparent envelopes. After asking for consent, the nurse opens the envelope assigned to the number that tells which group the subject is assigned to. Patients randomized to the new treatment practice are asked to give a sample which is analyzed with the POC device in the emergency room. If there are technical problems with the analysis, the nurse may take a new sample if necessary; a note on the technical problem is entered in the device log. During the trial, the number of technical problems with analysis increased, and the device manufacturer was informed of all tests that had failed. During the trial, over a short period from Sep 8 to 28, 2019, an increase in the number of failed samples was observed (9 out of 56, i.e. 16% of all samples analyzed). According to the manufacturer, this was to a significant degree (4 out of 9, 45%) associated with problems with the sample cassette transportation chain and wrong storage temperature during transportation. As technical problems persisted, the operating system of the POC test device was updated on Jan 7, 2020.

If an unforeseen adverse event occurs during sampling, an adverse event report is recorded in the hospital's internal adverse event reporting system; in addition, the investigators are informed of the event. The POC test results are automatically recorded in Weblab and are thus available at the doctor's appointment. Samples are only taken at the on-call physician's discretion from the children randomized to the current treatment group. The samples are stored in the emergency room and transported to the laboratory for analysis at 7 am the next morning. The results are entered into Weblab in the microbiology lab, and the on-call physician is responsible for reporting the results and reacting to them.

Due to the SARS-CoV2 epidemic and change in testing practices, randomization was halted on March 13, 2020 at 3 pm when 1,350 subjects had been recruited.

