## Secondary outcome measures

- Treatment with antibiotics initiated within a week (7 days) of the emergency room visit and different groups of antibiotics
- Macrolide antibiotics prescribed in the ED
- Macrolide antibiotics started in infants under 3 months (proportion)
- Immediate admittance to hospital from emergency room (hospitalized pediatric patients)
- Pediatric patients admitted to hospital within a week (7 days) of the emergency room visit
- Diagnostic tests performed in the emergency room
- Outpatient phone contacts and their number (with nurse or physician) within 7 days
- Revisits to emergency room within the next 7 days
- Ancillary laboratory testing
- Intensive care or intensive monitoring within the next 30 days after the emergency room visit
- Mortality within the next 30 days after the emergency room visit
- Visit associated costs
- Length of stay at ED
- Pathogen directed therapy (defined as antimicrobial therapy directed against detected pathogen with specific treatment available)
- Time from emergency room visit to onset of pathogen-directed treatment

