## 2.5.2. Control group

*Current treatment practice: The diagnostic tests needed are conducted in the laboratory during office hours following a clinical evaluation by the doctor who prescribed the test*

At the moment (since spring 2019), the following tests for respiratory tract pathogens are available in the emergency room of Oulu University Hospital. The tests are done in the laboratory and are prescribed by the on-call physician.

- Nucleic acid detection test for **influenza and RS virus**, analyzed in the laboratory; the results are available **approximately 2–3 hours** after sampling.
- In addition, since 2019, a test covering the most common **respiratory tract viruses as well as mycoplasma and pertussis**, which is done in the laboratory **during office hours** (Qiagen, Table 2)
- For both tests, the sample is most commonly taken from phlegm suctioned from the patient, or from the nasopharynx using a nylon or dacron swab.

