### 2.6.2. Secondary outcome measures

|          | Outcome                                                                                                                     | Definition of outcome in ClinicalTrials                                           |
|----------|-----------------------------------------------------------------------------------------------------------------------------|-----------------------------------------------------------------------------------|
| 1 | Treatment with antibiotics initiated within a week (7 days) of the emergency room visit and different groups of antibiotics | Proportion of children with antibiotics in one week                               |
| 2 | Macrolide antibiotics prescribed in the ED                                                                                  | Proportion of children receiving macrolide antibiotic at pediatric emergency room |
| 3 | Macrolide antibiotics started in infants                                                                                    | Proportion of infants aged < 3 months receiving                                   |

|    |                                                                                        |                                                                                                                               |
|----|----------------------------------------------------------------------------------------|-------------------------------------------------------------------------------------------------------------------------------|
|    | under 3 months (proportion)                                                            | macrolide antibiotic at pediatric emergency room                                                                              |
| 4  | Immediate admittance to hospital from emergency room (hospitalized pediatric patients) | Proportion of children admitted to hospital                                                                                   |
| 5  | Hospital admissions within a week after emergency room visit                           | Proportion of children admitted to hospital within one week after study entry                                                 |
| 6  | Other diagnostic tests performed in the emergency room                                 | Number of other diagnostic tests than point-of-care test performed at emergency room                                          |

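### The ED-only macrolide count in infants under 3 months normally captures result-triggered starts in the POC arm and normally misses them in controls; a labelled day-7 count should stand beside it

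*Combined protocol and SAP*

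**What the plan says.** **The outcome window.** Protocol 4.6 lists two macrolide outcomes next to each other. The all-age item is tied to the visit: "Macrolide antibiotics prescribed in the ED". The infant item is not: "Macrolide antibiotics started in infants under 3 months (proportion"). SAP 2.2.2 keeps the same contrast. In SAP 2.6.2 row 3 the outcome column again says started, but the registry column limits it to a "macrolide antibiotic at pediatric emergency room". SAP 5.2.3 analyses the registry version: "The counts and proportions of infants aged under 3 months to receive macrolide antibiotic prescription at ED will be reported".

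**When results arrive.** In the POC arm the result is due while the child is still in the ED (SAP 2.5.1). In the control arm the panel covering "respiratory tract viruses as well as mycoplasma and pertussis" is ordered at the physician's discretion and run in laboratory office hours (SAP 2.5.2), on weekdays (protocol 4.2). Protocol 4.5 adds: "The samples are stored in the emergency room and transported to the laboratory for analysis at 7 am the next morning". The study design paragraph of the protocol abstract puts the usual result time at the next working-day morning, and protocol 4.5 makes the on-call physician responsible for acting on it. The faster control test, at about 2–3 hours, covers only influenza and RSV.

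**What a result leads to.** The interpretation guide in Appendix 1 links a positive mycoplasma or pertussis finding to starting a macrolide, and a negative one to usually not giving it.

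**Other windows.** SAP 5.2.1 covers any antibiotic over a week: "The counts and proportions of participants to receive antibiotic prescription at ED and during following 7 days will be summarized and reported". SAP 5.2.2, for macrolides at all ages, is again limited to the visit: "The counts and proportions of participants to receive macrolide antibiotic prescription at ED will be reported".

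**The concern.** The arms differ by design in when a mycoplasma or pertussis result is known. An outcome window that closes at the end of the ED visit falls between those two times, so whether a result-triggered start is counted depends on allocation.

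This is the plan's only antibiotic-exposure outcome specific to its youngest children, and protocol 3.1 names macrolide harms (resistance, effects on the gut microbiome) as part of the motivation. If the ED-only figure is read as exposure, POC testing could appear to raise macrolide use in infants partly because control starts fell outside the count.

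The SAP pairs an ED window with a 7-day window for any antibiotic (5.1 and 5.2.1) and for hospital admission (5.2.4 and 5.2.5). It sets out no such pair for macrolides.

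**Working it through.** **No figure to reproduce.** The documents give no number of infants under 3 months, no pathogen prevalence, no control testing rate and no macrolide rate. The check is therefore a comparison of the texts, an algebraic form for the bias, and an illustration on assumptions.

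**Step 1: which starts are counted (SAP 5.2.3).**

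| Type of macrolide start | POC infant | Control infant |
|---|---|---|
| Empirical, at the ED | counted | counted |
| Triggered by a positive result | normally counted (result due during the visit) | normally missed (result usually next working day) |
| After the visit for any other reason | missed | missed |

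Only the middle row differs by arm.

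**Step 2: effect on the risk ratio.** Let p be the true proportion with a macrolide by day 7, equal in both arms. Let f be the fraction of control starts, and g the fraction of POC starts, that occur after the visit. Then

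apparent RR = p(1−g) / [p(1−f)] = (1−g)/(1−f), when the true RR is 1.

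| f | g | Apparent RR |
|---|---|---|
| 10% | 0 | 1/0.90 = 1.11 |
| 25% | 0 | 1/0.75 = 1.33 |
| 50% | 0 | 1/0.50 = 2.00 |
| 25% | 10% | 0.90/0.75 = 1.20 |
| 50% | 10% | 0.90/0.50 = 1.80 |
| 10% | 10% | 0.90/0.90 = 1.00 |

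Neither f nor g comes from the documents. The ratio exceeds 1 whenever f > g, which is what the result timing in the two arms leads one to expect.

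**Step 3: rough scale, on assumptions.** Protocol 4.5 gives 1,350 recruited; at 2:1 about 450 are controls. Assume infants under 3 months are 5–20% of them: 450 × 0.05 ≈ 22 to 450 × 0.20 = 90 control infants. Assume a prevalence q of mycoplasma or pertussis of 1–5%. Among positive controls, let e be the share given an empirical macrolide at the ED, t the share sampled, and m the share of known positives who are then started. Control starts are q·e at the ED and q·[e + (1−e)·t·m] by day 7. The share missed is (1−e)·t·m / [e + (1−e)·t·m].

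- e = 0.50, t = 0.30, m = 0.90: 0.135/0.635 = 21% missed.
- e = 0.25, t = 0.60, m = 0.90: 0.405/0.655 = 62% missed.
- e = 0, t = 0.90, m = 1.00: 0.90/0.90 = 100% missed.

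In children, the extremes are 22.5 × 0.01 × 0.135 = 0.03 and 90 × 0.05 × 0.90 = 4 control infants. These shares concern pathogen-positive infants only. Empirical macrolides in pathogen-negative controls are all counted at the ED and would bring f down.

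**Step 4: is it recovered elsewhere?** SAP 2.6.2 row 1 lists antibiotic groups within 7 days, so an all-age macrolide figure is implied, but SAP 5.2.1 does not set it out. Pathogen-directed therapy and time to it (SAP 5.2.14 and 5.2.15) are not specified for infants. No planned analysis gives macrolide starts after the visit in infants under 3 months.

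**The case against.** The strongest reply is that the ED window is the registered definition. SAP 5.2.3 follows the registry column, and the protocol item states no window at all, so it does not promise 7 days. A reader might infer that the SAP abandoned a 7-day outcome or departed from the registration. The documents show neither: the conflict is between wording without a limit and a registered wording with one. This stands, and it is a reason not to replace row 3 now that recruitment has ended.

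A reader might also infer that control exposure as such is missed. It is not: empirical ED macrolides in controls are counted, and protocol 3.1 describes macrolide starts as common although atypical pathogens are rare, which suggests that much use is empirical. An ED count is also a legitimate measure of the decision at the visit, including macrolides avoided after a negative result.

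Third, setting g to 0 is the extreme case. Protocol 4.5 reports 9 of 56 POC samples failing in one period, protocol 4.9 plans for results being in time for fewer than 70% of the POC arm, and SAP 4.4 lists device errors and missed samples as violations. Late POC starts pull the ratio towards 1. SAP 4.4 also lists immediate analysis of a control sample as a violation, so a few control results may arrive during the visit.

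Finally, a 7-day window does not equalise detection. All POC children are meant to be tested, controls only at discretion, so higher POC macrolide use could be a real effect of testing. That is correct, but the wider window would count such an effect alike in both arms.

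These points limit the claim and its size. They do not remove the arm-dependent counting of result-triggered starts.

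**Conclusion.** The concern holds for result-triggered starts. The ED-only comparison in infants under 3 months reflects when the result arrived as well as how many infants were exposed, and it tends to overstate POC use relative to control. This rests on three points in the documents: POC results due during the visit, control mycoplasma and pertussis results usually after it, and a guide that ties a macrolide to a positive result.

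The size cannot be estimated from the documents. The form (1−g)/(1−f) assumes equal true use and takes f and g as unknowns. A reader might take the value of 2.0 from Step 2 as the expected distortion, but that needs half of all control starts to come after the visit and no POC start to do so; nothing in the documents supports either figure. On the assumed ranges the loss is between almost none and about four control infants, so the estimate is likely to be imprecise under either window. The point is a worthwhile, low-cost improvement to a secondary outcome in a small subgroup. It does not touch the primary analysis.

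**What to change.** 1. Keep the registered ED-only proportion in SAP 2.6.2 row 3 and SAP 5.2.3.
2. Add to SAP 5.2.3 the proportion of infants under 3 months with a macrolide started from the index visit to day 7, ward starts included, by arm, with the difference, the risk ratio and 95% CIs. Label it as a post hoc addition: randomisation stopped on 13 March 2020, and SAP version 7.0 (March 2022) already holds analyses requested in review.
3. In SAP 5.2.1, report macrolides as a group within the 7-day analysis, as SAP 2.6.2 row 1 already lists.
4. State beside the ED-only figure that it reflects result timing as well as exposure.
5. Reconcile the wording of protocol 4.6, SAP 2.2.2, SAP 2.6.2 row 3 and SAP 5.2.3, so that each says whether the outcome is limited to the ED.

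**Cost.** No new data collection: SAP 2.10 follows participants for 30 days and takes prescriptions from hospital records and the national database. The work is some SAP wording and two table rows. The downside is two more comparisons without multiplicity adjustment, one of them in a small subgroup.
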